##### Physical activity levels

2.7.2.5

PA will be objectively assessed using an ActiGraph GT3x + accelerometer (ActiLife, version 6.11.7) worn on the hip for seven consecutive days during waking hours, excluding bathing, water activities, or sleeping. The accelerometer records acceleration in three axes, reporting the amount of activity performed at three intensity levels: light, moderate, and vigorous. Data will be processed using the open-source R package GGIR v.3.1–2. The processing pipeline includes: (i) auto-calibration of raw accelerometer data based on local gravitational acceleration (62), (ii) detection and imputation of non-wear time (63), and (iii) calculation of activity counts over 15-s epochs using the algorithm described by Neishabouri et al. (64) and facilitated in the open-source R package actilife counts (DOI: 10.5281/zenodo.7723333), and classifying MVPA as every epoch above the established cut-point for MVPA of 574 counts/15 s (65). Data will be aggregated by participant as the average daily time spent in MVPA during the baseline and follow-up assessments. In addition, PA will be self-reported using the Spanish Youth Activity Profile questionnaire a validated tool for estimating PA and sedentary behaviors at the group level in adolescents (kappa = 0.61–0.77; Intraclass Correlation Coefficient [ICC] = 0.77–0.89) (66). The Spanish version developed using a back-translation process, includes 19 items divided into three sections: (i) activity at school, (ii) activity out-of-school, and (iii) sedentary behaviors. The final variables to be analyzed will include average scores ranging from 1 to 5 for PA at school and PA outside of school, aggregated by participant during baseline and follow-up assessments.

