Despite the limited number of studies analyzing PAEE related to ACS, a significant gap remains in accurately assessing PAEE during free-living behaviors. Indirect calorimetry is widely recognized as the gold standard for measuring PAEE, as it directly quantifies oxygen consumption and carbon dioxide production, providing continuous, real-time data that capture the complex metabolic responses during activity (26). This direct measurement offers a significant advantage over methods that rely on predictive equations or self-reported data, which often oversimplify the dynamic and context-specific nature of free-living behaviors (26). Previous studies have frequently relied on stationary or semi-portable indirect calorimetry systems that are not well-suited for field applications (27). Although portable metabolic systems have been developed to facilitate outdoor assessments, their high cost and operational complexity limit their widespread use in educational and field contexts (27). As an alternative, researchers have employed established equations, such as those proposed by Riebe et al. (28) and Pandolf et al. (29). However, these equations were derived under highly controlled laboratory conditions (e.g., typically on treadmills) and, consequently, do not account for the variability of environmental factors (e.g., changes in speed, terrain, and weather), which critically influence PAEE in real-life settings, particularly in ACS (30). Another common practice for analyzing PAEE related to ACS has been through estimates based on counts measured by accelerometers (20, 31). However, accelerometers may not be the most appropriate devices for measuring PAEE in the context of ACS (32). Moreover, a recent study compared the PAEE associated with walking to that of using an e-scooter (33). However, this study was conducted under laboratory conditions, making it impossible to account for environmental factors that could influence PAEE. It is well known that the availability of safe and accessible routes directly correlates with increased PA among adolescents, which could, in turn, lead to higher PAEE (34). Additionally, PA levels may depend on adolescents’ perceptions in their commuting environment, considering factors such as fear of accidents, infrastructure, and social norms related to active commuting behaviors (35). Therefore, it is crucial to compare the PAEE associated with different modes of commuting to school in free-living conditions. Furthermore, developing a context-specific equation that incorporates key commuting characteristics (e.g., speed and distance) would provide a more accurate estimation of PAEE associated with this behavior.

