
**Table 1 tab1:** Schools’ inclusion and exclusion criteria.

Inclusion criteria	Exclusion criteria
The school has a specific space for parking bicycles and allows their parking	The school does not have specific infrastructure to park or store bicycles
The school has at least two classes per grade	The school offers bus transportation to the adolescents
At least eight students from the school will agree to participate in the study	The school is already participating in other interventions focused on promoting healthy behaviors
Schools from urban areas	The school has implemented an intervention to encourage commuting to school within the last year
	Schools from rural areas

**Table 2 tab2:** Participants’ inclusion and exclusion criteria.

Inclusion criteria	Exclusion criteria
Adolescents’ females and males aged from 12 to 17 years old (both ages included)	Adolescents younger than 12 years or older than 17 years
Healthy participants who can ride a bicycle safely and without difficulty.	Participants with any injury or medical condition that prevents safe participation in cycling to and from school
Be able to cycle to and from school at least 3 days per week during eight consecutive weeks (Intervention group)	Insufficient ability to ride a bicycle or inability to cycle to and from school at least 3 days a week (Intervention group)
Not to cycle to and from school more than 3 days a week during the last year	Participants who have cycled to and from school more than 3 days a week during the past year
To present a valid signed consent from their parents or legal guardians	Participants without a valid, signed parental or guardian consent form
To present valid data at baseline and follow-up from all the outcomes assessed	Participants who do not provide valid data for all assessed outcomes at baseline and follow-up

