#### Study assessment protocol

2.6.1

In Phase I, participants will perform three different simulations (i.e., commute by motorized-vehicle, walking, and cycling [see Figure 2]): (1) a simulation of driving to school will be performed by motorized-vehicle. After all the calibration process of the Cosmed K5 (both, flow and gas analyzers will be calibrated before every gas exchange measurement), a face-mask attached to the K5 will be place and gas exchange will be check during a two-minute period before the measurement start. After the check phase, gas exchange recording start during a five-minute period, while participants remain seated. Then, the participants will simulate commute in a motorized-vehicle by remaining seated in a chair for another 15-minute period, having previously walked for 2 mins simulating that participants are moving toward the motorized-vehicle from home. After this first simulation, there will be a five-minute period of cooling down. The total time of this first test will be 27 min. (2) A simulation walking to school will be conducted in a closed circuit defined by the research staff. The same procedures mentioned before will be followed. Then, the participant will walk for 15 min (the participant will determine the speed and intensity of walking) and finish with a five-minute cool down; (3) Participants will simulate a cycling route. They will wait for five-minute after walking and they will start cycling during 15-minute period along the designated route. The simulation will finish with a five-minute cool down period. The total time used in the walking and cycling simulations will be 45 min. These times were chosen because an average walking speed of 4.4–4.6 km/h would not exceed the distance Spanish adolescents are willing to walk to their educational center (1,350 m) (52). While no study in Spanish adolescents indicates the distance, they are willing to cycle to school, we estimated a distance of 4,200 m, the threshold distance used for Australian adolescents (53), with which a speed of approximately 15 km/h would not exceed 15 min. Detailed visual information on the evaluation and calibration process of the Cosmed K5 (Cosmed, Rome, Italy) can be found at the following link.^1^ In order that one active mode of commuting (e.g., walking) does not affect the post exercise oxygen consumption, thus PAEE, of the subsequent active mode of commuting (e.g., cycling), participants will alternate randomly by first performing the simulation of walking or cycling. In addition, the alternation of starting on the bike and walking will be counterbalanced by having the same number of participants starting on the bike or walking. Finally, all data will be downloaded using PC OMNIA.9 software v3.30.79 (Cosmed, Rome, Italy).

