The second part of the intervention will consist of an eight-week program cycling to and from school. The duration of 8 weeks for school cycling is appropriate in this setting according to a previous systematic review (47). During the eight-week intervention, adolescents will receive an encouragement strategy every week in the form of a challenge related to knowledge content about the importance of PA and having good physical condition for our health, benefits of ACS, knowledge of RMR, PAEE, and its importance, promotion of confidence and motivation for adolescents to travel safely in their environment. The functioning of these encouragement strategies, called Octopus Strategy, will consist of eight games that will be opened weekly as the intervention progresses. In each of the games a series of points will be obtained, and these will be accumulated so that there will be a competition between the different participating schools. The winner of the Octopus strategy will be the participant who completes all the games during the 8 weeks. It is important to highlight that although motivational strategies will be employed to support adherence to the intervention, they are not intended to address broader behavior change processes, such as altering participants’ attitudes or intentions toward active commuting. Thus, the Octopus strategy will aim to improve the adherence and motivation to the intervention (i.e., to cycle at least 3 days to and from the school). Table 4 shows a summary of the project’s objectives related to the *Bikeability* sessions and the contents to be developed in the encouragement strategies, during the eight-week intervention. More information about the different challenges proposed by our research group as an encouragement strategy in the Supplementary material and in the following link.^5^

**Table 4 tab4:** Eight-week school-based cycling intervention overview: octopus strategy.

Activity		Aim	Content	Instrument (target)
1 (week 1 and 2)	Training 1:Bikeability	2, 4 & 5	Implementation of the basic guidelines for bicycle maintenance, in addition to the rules for entry, exit and parking of the bicycle Knowledge and practice of cycling skills on a circuit closed to traffic Practice driving skills on closed circuits to traffic	Bicycles, helmets, first aid kits, cones, and whistle. Student skills evaluation sheet (adolescents/teachers)

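### Count-only MVPA from a hip accelerometer is likely to under-record the cycling that separates the arms, by an amount the protocol does not establish

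*Protocol article*

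**What the plan says.** Section 2.7.2.5 (Physical activity levels) fixes the objective outcome in detail. The accelerometer is "worn on the hip for seven consecutive days during waking hours", the processing ends by "classifying MVPA as every epoch above the established cut-point for MVPA of 574 counts/15 s", and the analysed variable follows: "Data will be aggregated by participant as the average daily time spent in MVPA during the baseline and follow-up assessments". No rule treats cycling epochs differently. The only other physical activity measure in that section is a questionnaire: "PA will be self-reported using the Spanish Youth Activity Profile questionnaire". It yields scores from 1 to 5, not minutes.

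The Introduction, discussing count-based estimates of the energy cost of commuting, says that "accelerometers may not be the most appropriate devices for measuring PAEE in the context of ACS".

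The intervention asks pupils "to cycle at least 3 days to and from the school" (section 2.8). The eligibility table limits prior cycling only ("Not to cycle to and from school more than 3 days a week during the last year"), so pupils who usually walk can enrol.

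Other data on the trips are planned. Accelerometer and GPS are issued on one belt (section 2.6.1, assessment day 2). The GPS also runs at a 15-second epoch (section 2.7.2.18), and heart rate is recorded on cycling trips (section 2.7.2.2). Section 2.7.2.18 uses GPS with accelerometry to estimate commuting PAEE. No section uses these data to classify MVPA.

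**The concern.** A hip device registers movement of the trunk. Walking moves the hip at every step, whereas seated pedalling moves it little, whatever the effort. This is mechanical reasoning and not a figure from the protocol. It means that one count threshold applied to all activity is likely to be least sensitive to the activity that the intervention adds. Because the two arms are meant to differ in cycling, any cycling the threshold misses does not cancel between them. It lowers the measured MVPA effect.

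At stake is how a null or negative MVPA result would be read. With count-only MVPA, the trial could not tell whether the programme failed to raise activity or the device failed to record it.

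**Working it through.** The protocol states no figure for this effect, so there is none to reproduce. The check asks how large the shortfall could be.

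**Inputs**
- Days cycled: 3 per week, the minimum in section 2.8.
- Trips per day: 2. The per-protocol definition in section 2.10.1 also admits one-way cycling. With one trip a day, every figure below halves.
- Trip length: 15 min, borrowed from the Phase I simulation ("they will start cycling during 15-minute period along the designated route") as an assumption for Phase II.
- Speeds in section 2.6.1: walking 4.4–4.6 km/h, cycling about 15 km/h.
- c, the share of cycling time credited as MVPA: not given, taken over 0 to 1.
- p, the share of cycled trips that replace a walk: not given, shown at 0 and 0.5.
- Also assumed: all cycling is truly MVPA, walks are recorded in full as MVPA, pupils cycle during the follow-up wear week, and there is no cycling at baseline or in the control arm. Eligibility allows some earlier cycling, so the added amount could be smaller.

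**No former walkers (p = 0)**

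Added cycling = 3 × 2 × 15 / 7 = 90/7 = 12.9 min/day. Recorded change = 12.9 × c. Shortfall = 12.9 × (1 − c).

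**Half former walkers (p = 0.5)**

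A 15-min walk at 4.5 km/h covers 1.125 km, and the same trip at 15 km/h takes 4.5 min. A former walker therefore loses 12.9 min/day of walking and gains 3 × 2 × 4.5 / 7 = 3.9 min/day of cycling, a true change of −9.0.
- True mean change = 0.5 × 12.86 + 0.5 × (−9.0) = +1.9 min/day.
- Mean cycling = 0.5 × 12.86 + 0.5 × 3.86 = 8.4 min/day.
- Mean walking lost = 0.5 × 12.86 = 6.4 min/day.
- Recorded change = 8.4 × c − 6.4. Shortfall = 8.4 × (1 − c).

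| c | p = 0: recorded (true +12.9) | p = 0: shortfall | p = 0.5: recorded (true +1.9) | p = 0.5: shortfall |
|---|---|---|---|---|
| 1 | +12.9 | 0 | +1.9 | 0 |
| 0.5 | +6.4 | 6.4 | −2.3 | 4.2 |
| 0.25 | +3.2 | 9.6 | −4.3 | 6.3 |
| 0 | 0.0 | 12.9 | −6.4 | 8.4 |

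The shortfall is downward for every c below 1. A negative recorded change needs former walkers as well: with half walkers it appears when c is below 6.43/8.36 = 0.77.

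**Illustration of power.** Read the sample-size section's f = 0.25 as d = 0.5, with 125 per arm, no clustering and no former walkers. If the true MVPA effect were that size, power would be 0.977 at c = 1, 0.507 at c = 0.5 and 0.166 at c = 0.25.

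**The case against.** The case on the other side has six parts, and much of it stands.

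- A reader might infer that the protocol itself declares the device unsuitable. It does not. The Introduction's remark is hedged and concerns PAEE, with no mention of hip placement, cycling or MVPA. The protocol also acts on it, since section 2.7.1.2 estimates cycling PAEE from equations using distance, speed and heart rate. The remark is relevant to a count-based intensity threshold but is not an admission about this outcome.
- A reader might infer that the cycling goes largely unrecorded. No document gives c, so likely under-recording is as far as the text and the mechanics allow.
- A reader might treat any fall in recorded MVPA among former walkers as a device error. At the protocol's own speeds their trips shorten, so much of the fall in minutes would be real. Swapping a 15-min walk for a 15-min ride would put the true change in the half-walker case at +6.4 min/day (12.9 × 0.5) instead of +1.9.
- The size depends on how much pupils cycle in the follow-up wear week. Section 2.7.2.2 mentions follow-up separately from the eight-week intervention period, and the figure showing the timing is not reproduced here.
- Epoch-level processing is often left to a fuller document. Here, however, the article fixes the MVPA rule down to the cut-point, and that rule makes no provision for cycling.
- Assigning intensity by travel mode has its own bias. It credits a group value and not the pupil's own measurement, mostly in one arm, so MVPA becomes partly a measure of adherence. This is a good reason not to replace the count-based outcome, but it does not argue against a companion analysis.

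**Conclusion.** The point holds as a likely downward bias in one secondary outcome. Its direction follows from the measurement rule whenever the cut-point credits less than all cycling time. Its size is unknown: 12.9 × (1 − c) min/day without former walkers, or about 8.4 × (1 − c) with half, under the trip length, frequency and wear-week assumptions above. The stronger reading, that the MVPA effect will come out null or negative, is not supported. A null result needs c near 0 or an offsetting loss of walking, a negative one needs enough former walkers relative to c, and the documents give neither quantity. RMR and the equation-based cycling PAEE are unaffected. The change is worth making because the data it needs are already planned.

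**What to change.** In section 2.7.2.5:

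1. Keep count-only MVPA and prespecify a second MVPA analysis beside it. In this analysis, epochs inside GPS-identified cycling trips are classified by the cycling intensity found in Phase I (K5 with heart rate). Apply the rule identically in both arms and at both time points.
2. Report from the Phase I accelerometer and K5 data what share of cycling time the 574-count cut-point credits as MVPA. This replaces the assumed c with an estimate from the study itself. Table 3 marks the accelerometer for Phase I, but section 2.6.1 does not say that it is worn during the simulations, so this should be stated.
3. State that count-only MVPA alone will not be used to conclude that cycling has no effect, or a negative effect, on physical activity.

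Table 3 as read here ticks GPS trip characteristics for Phase I only, whereas sections 2.6.1 and 2.7.2.18 collect GPS at baseline and follow-up. The table should be checked against the text, because the second analysis needs those data.

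The cost is extra data processing and wording, with no new device or visit. The downsides are reliance on intensities from about 50 Phase I volunteers and continued dependence on counts for days when the GPS signal is lost.

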##### Physical fitness

2.7.2.6

Cardiorespiratory fitness will be assessed using the validated Course Navette field test (67). Adolescents will run between two lines separated by 20 meters, maintaining a rhythm dictated by audio signals from a pre-recorded CD. The initial speed will be 8.5 km/h, increasing by 0.5 km/h per minute. The test will end when participants fail to reach the lines according to the audio cues for at least two consecutive trials or stop due to fatigue. The equations by Léger et al. (67), previously validated in children and adolescents (*r* = 0.587) (68), will be used to estimate maximum oxygen consumption (VO_2_max), calculated individually for each participant during baseline and follow-up assessments. Muscle strength of the upper and lower limbs will be evaluated using standardized and validated protocols (69, 70). Upper limb strength will be measured using an analog dynamometer (Takey TKK5401) following the ALPHA fitness battery recommendations. Participants will perform the test with both hands. Lower limb strength will be assessed using the Standing Long Jump (SLJ) test, a valid and reliable tool for measuring lower limb power (70). Both handgrip strength and SLJ presents a high association with isokinetic parameters (*r* = 0.61 and 0.87; R^2^ = 0.39 and 0.76, respectively) (71). Additionally, the mid-thigh pull test (IMTP) will be conducted, an isometric test of maximum leg and back strength performed with an analog dynamometer (Takei TKK5402). This test has been previously validated by considering different knee and hip positions, showing moderate reliability between positions (r ranging from 0.666 to 0.739) and high reliability between sessions (*r* > 0.819) (72). For all strength tests, measurements will be conducted twice with a two-minute rest between trials. Data will be averaged across trials and aggregated by participant during baseline and follow-up assessments.

##### Physical literacy

2.7.2.7

Perceived physical literacy will be evaluated using the Perceived Physical Literacy Instrument (PPLI). The PPLI has shown convergent validity ranging from 0.40 to 0.52, indicating that its three factors present adequate discriminant validity and moderate to good reliability (ICC = 0.62–0.79) (73). This tool consisting of nine items designed for adolescents and scored on a five-point Likert scale (1 = strongly disagree to 5 = strongly agree). The nine items are equally divided into three subscales: (a) knowledge and understanding (three items), (b) self-expression and communication with others (three items), and (c) sense of self and self-confidence (three items) (73). The final variable will be the mean score of the nine items aggregated by participant during baseline and follow-up.

##### Motor competence

2.7.2.8

Motor competence will be assessed using the Bruininks-Oseretsky Test (BOT-2; ICC >0.76 for all items) (74). The short form of the test will be used, consisting of 14 subtests that evaluate fine and gross motor skills. Fine motor tasks include Drawing, Lines through Winding Paths, Folding Paper, Copying a Square, Copying a Star, and Transferring Pennies. Gross motor tasks include Hopping on One Foot, Same-Side Synchronized Hopping, Heel-to-Toe Walking on a Line, Standing on One Leg and Balance Beam (Eyes Open), Stationary One-Legged Jumping, Catching a Ball with Both Hands, Dribbling a Ball, Alternating Hand Movements, Knee Push-Ups, and Sit-Ups. These tasks measure fine motor precision, bilateral coordination, balance, running speed, agility, upper body coordination, and strength (75). Results will be standardized using normative data from the BOT-2 Test Manual and aggregated by participant during baseline and follow-up assessments.

